## Abstract

**Background:**

Low-dose computed tomography (lung cancer screening) can reduce lung cancer-specific mortality by 20–24%. Based on this evidence, the United States Preventive Services Task Force recommends annual lung cancer screening for asymptomatic high-risk individuals. Despite this recommendation, utilization is low (3–20%). Lung cancer screening may be particularly beneficial for African American patients because they are more likely to have advanced disease, lower survival, and lower screening rates compared to White individuals. Evidence points to multilevel approaches that simultaneously address multiple determinants to increase screening rates and decrease lung cancer burden in minoritized populations. This study will test the effects of provider- and patient-level strategies for promoting equitable lung cancer screening utilization.

**Methods:**

Guided by the Health Disparities Research Framework and the Practical, Robust Implementation and Sustainability Model, we will conduct a quasi-experimental study with four primary care clinics within a large health system (MedStar Health). Individuals eligible for lung cancer screening, defined as 50–80 years old, ≥ 20 pack-years, currently smoking, or quit < 15 years, no history of lung cancer, who have an appointment scheduled with their provider, and who are non-adherent to screening will be identified via the EHR, contacted, and enrolled (*N* = 184 for implementation clinics, *N* = 184 for comparison clinics; total *N* = 368). Provider participants will include those practicing at the partner clinics (*N* = 26). To increase provider-prompted discussions about lung screening, an electronic health record (EHR) clinician reminder will be sent to providers prior to scheduled visits with the screening-eligible participants. To increase patient-level knowledge and patient activation about screening, an inreach specialist will conduct a pre-visit phone-based educational session with participants. Patient participants will be assessed at baseline and 1-week post-visit to measure provider-patient discussion, screening intentions, and knowledge. Screening referrals and screening completion rates will be assessed via the EHR at 6 months. We will use mixed methods and multilevel assessments of patients and providers to evaluate the implementation outcomes (adoption, feasibility, acceptability, and fidelity).

**Discussion:**

The study will inform future work designed to measure the independent and overlapping contributions of the multilevel implementation strategies to advance equity in lung screening rates.

**Trial registration:**

ClinicalTrials.gov, NCT04675476. Registered December 19, 2020.

Contributions to the literature
Low-dose computed tomography (lung cancer screening) can reduce lung cancer-specific mortality by 20–24%, But utilization is low (3–20%)Lung cancer screening may be particularly beneficial for African American patients because they are more likely to have advanced disease, lower survival, and lower screening rates compared to White individuals.This study will test the effects of provider- and patient-level strategies for promoting equitable lung cancer screening utilization.This study is guided by the NIH Health Disparities Framework and uses mixed methods to evaluate the impact of multilevel implementation strategies on lung screening rates between African American and White patients.

## Background

The United States (US) Preventive Services Task Force (USPSTF) recommends annual lung cancer screening for asymptomatic individuals aged 50 to 80 years who have a ≥ 20 pack-year smoking history and currently smoke or have quit within the past 15 years (Grade B) [1]. Based on a systematic review of the evidence, including two large randomized controlled trials, the USPSTF concluded that screening high-risk individuals via low-dose computed tomography (CT) can reduce lung cancer mortality and may reduce all-cause mortality [1]. These trials included the National Lung Screening Trial (NLST), which reported that compared to chest X-ray, annual low-dose CT resulted in a 20% lung cancer-specific mortality reduction among individuals at high risk for lung cancer [2], and the Dutch NELSON trial, which demonstrated a 24% lung cancer mortality reduction among men who were screened versus not screened [3]. Despite the initial USPSTF recommendation released in 2013, the available estimates indicate screening uptake remains low, ranging from 3% in 2015 to 6.5–20% in 2019–2020 [4–6]. While the expanded criteria in 2021 increased the number of lung cancer screening-eligible individuals from 8 million to 14.5 million [7], barriers may still persist in the uptake of lung cancer screening [8].

Racial disparities in lung cancer predominantly affect Black or African American individuals (African Americans) in the US. Although African Americans smoke fewer cigarettes per day than White individuals (Whites), there are persistent differences in lung cancer rates between these groups [9]. African American men have the highest lung cancer incidence and death rates compared to all racial and ethnic groups. Relative to their White counterparts, African American women are at a lower risk of getting the disease, but have comparable cancer death rates [9]. Additionally, African Americans are diagnosed with lung cancer at an earlier age compared to Whites [10].

There are several drivers of lung cancer health disparities, including forms of oppression that span across the cancer continuum and occur at multiple levels (e.g., individual, societal) [11]. This includes differences in exposure to risk factors (e.g., greater exposure to air pollution and tobacco smoke), lack of insurance and barriers to healthcare access, historical medical racism and medical mistrust, discrimination within the healthcare system including differential discussion based on a patient’s race, and underrepresentation in clinical trials that inform the development of screening guidelines and novel therapies. It is also well documented that the tobacco industry has used long-standing predatory practices to target minoritized groups resulting in greater tobacco exposure and tobacco-related disparities, including lung cancer [12].

Lung cancer screening may be particularly beneficial for African Americans because they are more likely to have advanced disease and lower survival compared to Whites [13]. Additionally, data from the NLST suggested that lung cancer screening reduces lung cancer mortality to a greater extent in African Americans compared to all racial groups (hazard ratio, 0.61 vs. 0.86) [14]. However, lung cancer screening rates are consistently low across all racial and ethnic groups [6], and data suggest rates of uptake are lower among African Americans compared to Whites [15–17]. In the context of lung cancer screening, there are several factors that may contribute to racial disparities including (1) current screening guidelines do not take into account additional risk factors and differences in smoking patterns among individuals who may benefit from early detection, (2) socially disadvantaged areas that contribute to a higher smoking rate and higher lung cancer incidence, but have fewer accredited screening facilities creating an access issue, and (3) medical mistrust and the smoking-related stigma that can stand in the way of seeking screening or other forms of medical care [18]. Evidence points to the need for multilevel methods that simultaneously address multiple determinants to increase screening rates and decrease lung cancer morbidity and mortality in minoritized populations [19–21].

The National Institute on Minority Health and Health Disparities (NIMHD) Health Disparities Research Framework emphasizes the importance of using multilevel approaches to address disparities [22]. The framework identifies multiple health determinants, including behavior (e.g., preventive health behaviors, tobacco use exposure) and healthcare systems (e.g., systemic bias, patient-provider communication) that result in racial disparities in health outcomes. Within the lung cancer screening context, there are determinants at the *healthcare system-level* (e.g., lack of investment by health systems to identify lung cancer screening eligible patients); at the *provider-level* (e.g., provider time constraints, lack of familiarity with screening criteria, and racial bias); and at the *patient-level* (e.g., low awareness and knowledge about lung cancer screening, smoking-related stigma, and medical mistrust) [15, 18, 23]. There is a growing body of literature of multilevel interventions and implementation strategies that show promise in improving health outcomes and advancing health equity [21]. However, to date, there have only been four multilevel studies conducted on lung screening [24–27]. In a multilevel intervention that used best practice alerts and trainings for providers as well as marketing and patient navigation with language interpreters, they increased the number of lung cancer screenings compared to baseline with the highest rates among Hispanic patients, followed by Black patients, and non-Hispanic White patients [24]. Other studies have used system- and provider-level implementation strategies including automated reports and utilizing nurse practitioners to schedule and enroll patients into the screening program [25–27]. Colamonici and colleagues found an immediate and sustained increase in weekly lung cancer screening referrals by targeting providers and patients, but these studies noted barriers to successful implementation including implementation characteristics (e.g., organizational readiness, patient needs, and resources) and the need for future multisite projects [25–27].

Inreach is the process of identifying potentially eligible individuals within a clinic or health system via the EHR and attempting to connect them with evidence-based care [28]. Inreach, typically conducted by a screening program navigator or coordinator, is an approach that has been used widely in clinical settings and found to be effective for other screening types, such as colorectal, breast, and cervical cancers [29–32]. While there is currently a lack of research focusing on the utility of inreach for lung cancer screening, two studies used methods for identifying eligible patients in order to provide educational classes and interactive screening decision aids. They found these strategies can increase lung cancer screening-related knowledge and behaviors [32, 33]. In order to target key barriers to lung cancer screening at the patient-level, this study will utilize inreach to identify potentially eligible individuals via the EHR ahead of an upcoming clinic visit. Trained health education specialists will educate patients about lung cancer screening and promote patient activation for the individual to discuss screening at their next visit. The concept of patient activation has been used widely and it empowers patients to obtain the skills, knowledge, and motivation to participate as a member of the care team [34, 35]. Thus, the patient component will target lung screening knowledge and awareness along with other barriers (e.g., smoking-related stigma, medical mistrust) to encourage patient-provider discussion.

Clinician reminders are one of the Expert Recommendations for Implementing Change (ERIC) discrete implementation strategies that prompt clinicians to recall information or use a clinical innovation, like evidence-based screening recommendations. In general practice, provider prompts and best practice alerts have been effective in promoting evidence-based and guideline-concordant care. However, providers have reported “alert fatigue” suggesting that reminders are ignored [36–38]. To date, three studies have been conducted to evaluate the impact of clinician reminders on lung screening referrals and have found these to be effective approaches to improving lung cancer screening in primary care [24, 39, 40]. A pre-visit planning message is a type of clinician reminder that aims to help the provider conduct the clinic visit more effectively by gathering information ahead of time so they can devote more attention during the visit to discussing that information and responding to the patient’s questions. An advantage of this type of reminder is that it is not disruptive to the provider’s workflow like pop-up alerts may be. This type of clinician reminder may be especially important for lung cancer screening, because to be eligible for coverage, the Centers for Medicare & Medicaid Services guidelines require a shared decision-making visit [41]. This visit is required to be conducted by a healthcare provider with the patient prior to the first screening referral to discuss the benefits, risks, and limitations of screening, and smoking cessation. To address provider time constraints about lung screening, this study will send a pre-visit planning message as a reminder to discuss screening with eligible patients.

This study is guided by the Practical, Robust, Implementation & Sustainability (PRISM) Model, which includes the Reach, Effectiveness, Adoption, Implementation, Maintenance (RE-AIM) Framework [42, 43]. The planned trial will assess the effectiveness and feasibility of the multilevel implementation strategies to improve lung cancer screening utilization and to address racial disparities (Fig. 1). PRISM expands upon the RE-AIM framework and contains two parts: the contextual factors at individual and organizational levels and the RE-AIM outcomes. In this study, we will use RE-AIM to quantify the reach as measured by percent of providers and percent of patients offered study enrollment, effectiveness (screening outcomes), adoption (% providers who open EHR messages), and implementation (feasibility, acceptability, fidelity). This study will use mixed methods to conduct semi-structured interviews before (pre-) and after (post-) trial with MedStar leadership, referring providers, clinic staff, and participants.

**Fig. 1 Fig1:**
[figure not shown]
Conceptual framework

## Methods/design

### Study aims

This study will target provider- and patient-level barriers in order to improve utilization of lung screening and to achieve equity in screening rates by conducting a quasi-experimental study comparing a Multilevel Intervention to Usual Care. The Multilevel Intervention will perform inreach to educate patients about screening prior to their visit. At the same time, an EHR communication tool, similar to email, will send a reminder to primary care providers prior to scheduled visits with screening-eligible patients.

The *specific aims* of the trial are to (1) test the impact of the multilevel strategies on primary outcomes (provider-patient discussion, screening intentions, and knowledge) and secondary outcomes (screening referrals and screening completion rates) and (2) evaluate the implementation outcomes (adoption, feasibility, acceptability, fidelity).

The *hypotheses* are (1) participants in the Multilevel Clinics who receive the provider- and patient-level strategies will be significantly more likely to report having a screening discussion, intending to be screened, and having greater knowledge compared to the Comparison Clinic participants; (2) the multilevel, bundled strategies will increase screening referrals made by providers in the Multilevel Clinics; and (3) completion rates among the participants will be higher among the Multilevel Clinic participants compared to the Comparison Clinic participants. Finally, we will explore whether Health Disparities Framework factors (e.g., race, education, health literacy) moderate the outcomes (e.g., we expect that African Americans will have significantly greater knowledge in the Multilevel Clinics vs. the Comparison Clinics, whereas the strategies will have less of an impact among Whites).

### Clinical setting and healthcare provider participants

MedStar Health, the largest not-for-profit health system in the Mid-Atlantic, includes more than 300 care locations including more than 60 ambulatory care centers, and primary and specialty care in academic medical centers and community-based clinics, 10 hospitals, and 33 urgent care clinics located in Baltimore, MD, Washington, DC, and Northern VA. This health system provides care to a diverse community which includes a large Black or African American population (44–73% in the participating clinics), and uninsured or underinsured individuals.

We will conduct the quasi-experimental study in partnership with four primary care, community-based ambulatory clinics within the MedStar Health system, matched on CT scanner on site (yes/no) and minority representation (> 40% Black or African American; Fig. 2). Clinic eligibility criteria include (1) clinic providers use the Message Center within MedConnect (Oracle Cerner); (2) > 400 patients who are 50–80 years old with a documented smoking history in the last 12 months; (3) > 40% African American patient population; and (4) a site champion who will serve as the primary point of contact for this study. The provider sample includes full- and part-time primary care providers at the participating clinics.

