### Patient recruitment and procedures

During the recruitment period, the research assistants will access the list of potentially eligible individuals from an EHR report that our team developed to identify patients with an upcoming visit who are 50–80 years old with an ever-smoking history. Due to the limitations of the EHR smoking history data, including a large number of missing data for the pack-years field (90% on average are missing pack-years), we are conservatively estimating 25% of those reached will be eligible for the study (Fig. 2). The report utilizes EHR appointment and clinical data and will be imported into the study’s REDCap database weekly by the study team. Our team will invite patients to participate in the study through a mailed invitation letter, email, and the myMedStar patient portal, followed by phone calls (up to 3 attempts). During this call, the research staff member will describe the study, determine eligibility, obtain verbal consent, and complete the baseline assessment. We expect to enroll *n* = 184 in the Multilevel Clinics and *n* = 184 in the Comparison Clinics (total *N* = 368).

Following baseline (T0), Multilevel Clinic participants will receive the phone-based inreach and education within 1 week to 3 days prior to the visit. The comparison clinics will not receive the bundled strategies, but eligible participants will be enrolled and followed to measure the outcomes. All patient participants will receive up to $50 in total for their participation.

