This study will provide preliminary data on the effectiveness and feasibility of multilevel implementation strategies to improve lung screening utilization in an equitable manner. Future work will include a large 2 × 2 factorial, cluster randomized trial to compare the independent and overlapping contributions of the provider and patient implementation strategies. Study limitations include the quasi-experimental study design, which will limit the ability to determine causality. Second, we considered recruiting all potentially eligible patients irrespective of having an upcoming appointment, as those with a scheduled appointment may be sicker and/or more engaged in their healthcare. However, a primary endpoint is whether the provider-level prompt and the patient-level activation impact the discussion about lung screening at the clinical encounter, and so we elected to include an upcoming appointment as an eligibility criterion. It is well documented that the collection of smoking-related data (e.g., smoking duration, cigarettes per day, pack-years) in the EHR is not standardized and is often incomplete. The proposed study will use the EHR data to identify potentially eligible individuals based on age (50–80 years old) and smoking status (current and former). However, there will be a high number of screen failures as well as patients who may be eligible for lung screening but are not approached for the study due to data missingness. In other ongoing work, our research team is conducting a quality improvement project to improve how tobacco use is assessed and documented in the primary care setting across MedStar.

Following the successful completion of this study, future work will include partnering with an expanded number of primary care practices and utilizing a cluster randomized controlled trial to determine if these implementation approaches facilitate an increase in lung screening rates equitably.

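### The clinics are described as matched on minority representation, but the only stated level (> 40%) is also an eligibility criterion, so the matching as written secures no balance on race between arms

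*Protocol article*

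**What the plan says.** All the clinic statements are in the protocol article, section Clinical setting and healthcare provider participants. The study uses "four primary care, community-based ambulatory clinics within the MedStar Health system", and these are "matched on CT scanner on site (yes/no) and minority representation". The second factor is defined only as "minority representation (> 40% Black or African American; Fig. 2". The next sentence lists the clinic eligibility criteria, and the third is "3) > 40% African American patient population". The section also reports a "large Black or African American population (44–73% in the participating clinics". It does not give each clinic's share, the pairs, or which clinics are in which arm.

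Patient recruitment and procedures plans 184 patients "in the Multilevel Clinics and *n* = 184 in the Comparison Clinics (total *N* = 368". The Statistical analysis plan section enters a baseline variable as a covariate only when it is significantly associated, at 0.05, with both study arm and the outcome in question. Race is also named as a potential moderator, to be explored through an interaction with arm. The Discussion concedes: "Study limitations include the quasi-experimental study design, which will limit the ability to determine causality".

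**The concern.** A matching factor is useful only if clinics can differ on it. Here the cut used for matching is the cut used for entry, so the factor takes one value across all eligible clinics and cannot guide any pairing. The real variation, 44% to 73%, lies entirely above the cut and is ignored by it.

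This matters more here than it would in a randomised trial. Four clinics are compared without any described random allocation, and matching is the only design-stage protection against clinic differences that the article names. Race is also central to the study: the aims seek equity in screening rates, one hypothesis expects a larger knowledge effect among African Americans, and the Background says uptake is lower among them. A reader told that the arms are matched on minority representation will assume they are comparable on it. The stated rule does not provide that, and the main arm models bring race in only when the significance screen does.

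**Working it through.** **1. The two statements side by side.** Matching level: > 40% Black or African American. Eligibility criterion 3: > 40% African American. The lowest participating clinic is at 44%, so all four fall in the same category. Every possible split of the clinics satisfies the factor. Only CT scanner on site can separate clinics.

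**2. How far apart the arms could be.** Inputs from the article: four clinics, minimum 44%, maximum 73%. Assumptions: two clinics per arm, equal weights, and clinic share standing in for the share among enrolled patients. Let the other two clinics have shares a and b, each between 44 and 73.

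- Extreme clinics in opposite arms: gap = |(73 + b)/2 − (44 + a)/2|. This runs from 0 (a = 73, b = 44) to 29 (a = 44, b = 73). It is (73 − 44)/2 = 14.5 when a = b.
- Extreme clinics in the same arm: gap = |(73 + 44)/2 − (a + b)/2| = |58.5 − (a + b)/2|. This runs from 0 to 14.5.

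The supported range is therefore 0 to at most 29 points. An illustrative middle case is shares of 44, 55, 62 and 73 with the two lowest against the two highest: 67.5 − 49.5 = 18 points.

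**3. What a gap could do.** Unadjusted bias = gap × racial difference in the outcome. The article gives no racial difference for knowledge, discussion or intentions, so this part is assumed. For knowledge, with an 18-point gap:

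| Assumed racial difference | Bias | Share of the 0.33 target effect size |
|---|---|---|
| 0.2 SD | 0.18 × 0.2 = 0.036 SD | 11% |
| 0.3 SD | 0.18 × 0.3 = 0.054 SD | 16% |
| 0.5 SD | 0.18 × 0.5 = 0.090 SD | 27% |

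**4. How often the 0.05 screen admits race.** Take 184 per arm, race in two groups, shares of 49.5% and 67.5%, and no treatment effect.

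- Race with arm: SE = √[(0.495 × 0.505 + 0.675 × 0.325)/184] = 0.0505, z = 0.18/0.0505 = 3.56, power = Φ(3.56 − 1.96) = 0.946.
- Race with outcome at 0.3 SD: group sizes are about 215 and 153, SE = √(1/215 + 1/153) = 0.106, z = 2.84, power = Φ(2.84 − 1.96) = 0.81.
- Both: 0.946 × 0.81 = 0.77. Simulations of 4,000 trials gave 75% to 77%. Race is missed in roughly a quarter of trials.

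The same calculation gives 45% admission at 0.2 SD and 94% at 0.5 SD. At a 29-point gap and 0.5 SD it gives 99.7% (99.6% when simulated).

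A real treatment effect shifts these figures, because the screen looks at race and outcome without regard to arm. With a true effect of 0.33 SD and more of the lower-scoring group in the intervention arm, simulated admission at an 18-point gap falls to 24% (0.2 SD) and 55% (0.3 SD). In the opposite direction it rises to 63% and 87%.

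**The case against.** The strongest reply is that this is a wording slip with little behind it. Four parts of that reply stand.

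- **The arms may be well balanced.** The CT-scanner factor restricts the splits. If 44 and 55 form one CT pair, 62 and 73 the other, and each pair is divided between arms, the largest gap is (55 + 73)/2 − (44 + 62)/2 = 11 points, not 18. With shares of 44, 44, 73 and 73 paired the same way, it is 0. Fig. 2 is cited in the matching statement and is not shown, so it may display a closer pairing.
- **The screen works best where the bias is largest.** A reader might multiply the 29-point maximum by a 0.5 SD difference and quote 0.145 SD, or 44% of the target effect. In that case race is admitted almost always, so the main model would adjust for it. The exposure is mainly to small or moderate racial differences.
- **Race is not absent from the models otherwise.** The moderator analyses fit race with arm whatever its p-value, though only as exploratory interaction models and not as the main comparison.
- **The article is open about its limits.** It prints the 44–73% range and says the design limits causal conclusions.

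A reader might also infer that the arms must differ by about 15 points or more. They need not: 14.5 is the value in one arrangement, and the minimum is 0. Nor does the article show that the clinics were unpaired in practice. What the reply does not remove is the redundancy itself: as printed, the cut cannot match anything.

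**Conclusion.** The point holds as a defect in a stated design property. Matching on minority representation, as defined, adds nothing to eligibility and does not secure balance between arms. The arm difference in African American share could be anywhere from 0 to at most 29 points, assuming two equally weighted clinics per arm and clinic share close to enrolled share.

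The consequence for the results is conditional and probably modest. With an assumed 0.3 SD racial difference and an 18-point gap, the bias is about 0.05 SD before adjustment. The planned screen then misses race in roughly a quarter of trials when there is no treatment effect, and more or less often when there is one, depending on its direction. The documents do not establish that the arms are imbalanced or that the results will be biased. They show only that neither the matching rule nor the covariate rule guarantees protection on race. A correction is worthwhile because clinics are not described as randomised, race is the equity variable, and the remedy is almost free.

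**What to change.** Describe the clinics as matched on CT scanner on site only, and leave the > 40% level where it belongs, among the eligibility criteria. If the actual percentages were paired, say so and state the pairing.

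Pre-specify patient race as a covariate in every primary and secondary arm model, whatever its p-value, instead of leaving it to the 0.05 screen. Race is already collected at baseline in three categories, so this adds one covariate with two indicator terms. The moderator analyses can stay as they are.

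The cost is that covariate and a design description that reads slightly less favourably. Adjusting for patient race addresses differences in racial mix between arms. It does not remove other differences between the clinics, which the acknowledged limits of the quasi-experimental design still cover.
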